#### Data Analysis: Secondary Outcomes

Data from all participants will also be used to determine the cumulative incidence of illness symptoms in travelers returning from Bali. The impact of demographic factors, risk prevention behaviors, and knowledge on the risk of travel-related illness symptoms in the study population will be analyzed using logistic regression.

Data from the control group will be used to assess further secondary outcomes. A difference in self-reported illness, risk prevention behaviors, and health risk knowledge between those that sourced PTHA independently—external to the study—and those who did not receive any PTHA will be assessed. In addition, self-reported illness symptom rates in travelers returning from Bali will be determined.

The proportion of travelers in the control group that received PTHA from an alternative source, the source of this travel advice, and differences in demographic groups will be compared between travelers who reported illness and those who did not.

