#### Cost-of-Illness Analysis

Data from all participants in this study will be used to estimate the cost of travel-related illness in Western Australian travelers to Bali. The cost-of-illness analysis will be carried out using the framework described by Abelson et al [22] to determine the cost of foodborne illness in Australia and New Zealand [23,24]. Costs measured in this analysis will be direct health care costs—including doctor visits, hospitalizations, medical evacuations, and laboratory tests, both in Bali and Australia—and indirect health care costs—including indirect non-health care costs (eg, workdays lost).

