#### Sample Size Calculation

The sample size calculation was based upon the online PTHA intervention lowering the rate of self-reported illness in Western Australians returning from Bali by 10%. Existing literature suggests that reduction in illness as a result of visiting a travel doctor before departure is approximately 20% [13,14]. The sample size calculation assumed an illness rate of 40% in the control group [3], with a reduction of 10% in the intervention group, detected at 80% power with a *P* value of .05. A sample size of 712 participants completing the study—356 control and 356 intervention participants—was determined using PS: Power and Sample Size Calculation statistical software [25]. Assuming approximately 50% of participants are lost at follow-up, which is the average for Internet-based trials [26], and although we expect less loss because of the incentive, at least 1424 participants—712 exposed and 712 unexposed participants—would need to be enrolled in the study.

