### Strengths and Limitations

There are multiple benefits to using our proposed study design for this project. It will be possible to simultaneously determine base rates of illness and compare existing PTHA practices (ie, PTHA sourced by the participants independently) and a novel intervention.

Limitations include the potential exclusion of those travelers without access to, or unfamiliarity with, a computer or mobile phone; however, 87% of WA travelers to Bali used the Internet to purchase flights and/or accommodation [20]. Also, 2015 social media statistics report that 82% of Australian Internet users use Google and 60% use Facebook each month for around three and eight hours, respectively [28]. In addition, the PTHA intervention is targeted to, and intended for use by, Internet-savvy consumers.

It is possible that participants with an interest in health will be more likely to enroll in this study. This may lead to an over-reporting of PTHA-seeking and risk-prevention behaviors. To minimize this effect, the online advertising and study enrollment webpage will have an emphasis on the Bali travel experience more generally and will not highlight the health risks associated with travel to this destination. In addition, the results from this study will be compared to the results from the 2014 airport survey previously undertaken by our group, which used different methodology. The demographics of the two study cohorts will be compared to determine how the online cohort compares to the cohort recruited at the airport. Participants may also claim more “favorable” health-seeking behaviors when providing health information to a health authority. To reduce this effect, the surveys have been designed to be self-administered.

The cost-of-illness analysis has several limitations. While every effort will be made to follow up with participants who report visiting a health care professional about their illness, this may not always be possible. The participant may decline to provide their information, this information may be incorrect, and some health care professionals may decline to provide the required information. In addition, if the participant has reported illness with ongoing treatment, it may be difficult to determine an accurate cost.

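### The plan gives two sources for one illness rate, and the pooled one falls below the rate without the video by half of whatever effect the video has

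*Protocol article*

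**What the plan says.** All places are in the Protocol article.

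- Data Analysis: Secondary Outcomes, first paragraph: "Data from all participants will also be used to determine the cumulative incidence of illness symptoms in travelers returning from Bali".
- Same section, second paragraph. It opens by assigning its analyses to the control group, sets out the comparison of controls who did and did not find their own advice, and closes: "In addition, self-reported illness symptom rates in travelers returning from Bali will be determined". This closing sentence names no arm. Only its position ties it to the controls.
- Cost-of-Illness Analysis: "Data from all participants in this study will be used to estimate the cost of travel-related illness". The stated target is Western Australian travellers to Bali. The section does not say whether cost will be per ill case, per traveller or scaled to the population.
- Strengths and Limitations: "It will be possible to simultaneously determine base rates of illness". No population is named.
- Randomization and Intervention: allocation is 1:1, and only the intervention group is given the video.
- Sample Size Calculation: "The sample size calculation assumed an illness rate of 40% in the control group", with a 10% reduction in the intervention group.

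No weighting, reporting by arm or condition on the trial result is stated for the pooled incidence or the cost.

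**The concern.** The descriptive aims concern Western Australians who travel to Bali, and these travellers do not ordinarily receive the study video. A rate from both arms together is a mixture whose weights come from the allocation ratio and from completion in each arm. If the video lowers illness, the mixture lies below the rate in travellers without it.

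The same section then appears to take this rate from controls alone. Two figures could be reported under one description, with nothing to say which is the base rate. The Introduction and Discussion both stress how little is known about illness burden in these travellers, so the figure may well be cited by itself. A cost per traveller or for the population would inherit the choice of rate.

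**Working it through.** **Inputs.** From Sample Size Calculation: control rate 40%, reduction 10%, power 80%, alpha 0.05, and "356 control and 356 intervention participants" completing. From Randomization: 1:1 allocation.

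**1. Which effect did the plan use?** For two proportions, two-sided, without continuity correction:

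n = [1.96 × √(2 × 0.35 × 0.65) + 0.842 × √(0.40 × 0.60 + 0.30 × 0.70)]² / 0.10² ≈ 356 per arm.

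This matches the stated figure. A relative 10% reduction (40% versus 36%) would need 2311 per arm. The planned effect is therefore 10 percentage points, 40% versus 30%.

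**2. Pooled rate.** With equal completion by arm, pooled = (p_c + p_i)/2, so bias as a no-video rate = −(p_c − p_i)/2, which is half the effect.

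**3. Precision with 356 completers per arm.**

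- Control arm only: 1.96 × √(0.40 × 0.60/356) = 5.1 points.
- Pooled, at 40% versus 30%: 1.96 × ½ × √((0.24 + 0.21)/356) = 3.5 points.

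**4. Results over a range of effects** (control rate 40%; RMSE is root mean squared error, √(SE² + bias²)):

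| Intervention rate | Pooled rate | Bias, points | Relative bias | Pooled 95% half-width, points | Chance that pooled interval covers 40% | Pooled RMSE, points |
|---|---|---|---|---|---|---|
| 40% | 40% | 0 | 0% | 3.6 | 95% | 1.8 |
| 36% | 38% | −2 | −5% | 3.6 | 80% | 2.7 |
| 32% | 36% | −4 | −10% | 3.5 | 39% | 4.4 |
| 30% | 35% | −5 | −12.5% | 3.5 | 20% | 5.3 |

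The control-only RMSE is 2.6 points throughout.

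**5. Break-even.** Pooling has the smaller mean squared error while (d/2)² < 0.24/356 − (0.24 + p_i(1 − p_i))/(4 × 356), where d is the true effect and p_i = 0.40 − d. This gives d below about 3.7 points.

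**6. Unequal completion (assumed splits).** If 60% of controls and 40% of the intervention arm complete, the pooled rate at 40% versus 30% is 0.6 × 40% + 0.4 × 30% = 36%. With the split reversed it is 34%.

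**7. Cost.** Cost per traveller = incidence × cost per ill case. If cost per case is equal by arm (an assumption; no cost figures are given), the pooled incidence changes cost per traveller by 35/40 − 1 = −12.5%, and cost per ill case does not change. Expected ill cases available for costing are 0.40 × 356 + 0.30 × 356 ≈ 249 from both arms, against 0.40 × 356 ≈ 142 from controls alone.

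**The case against.** Several points on the other side stand.

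- **The control-arm rate may already be planned.** If the closing sentence of the control-group paragraph means controls, the rate without the video will be produced, and the promised base rates can come from it. The pooled sentence does not use the phrase base rate. Two figures for two populations do not by themselves contradict each other. This reduces the point on incidence to a failure to say which figure is the headline. It does not remove it, because both are described as rates in travellers returning from Bali. If the sentence does not mean controls, it repeats the first paragraph and only the pooled rate is planned.
- **The bias depends on the effect.** It is zero if the video does nothing, and below about 3.7 points of effect pooling is the better estimator on mean squared error. The intervention is an emailed link to a video of about three minutes, so a small effect is plausible. The 5-point figure rests on the plan's own design assumption.
- **The cost section does not fix the quantity.** A reader might infer that the cost of illness will be 12.5% too low, or that pooling should be removed from the cost analysis. The document supports neither. It does not say that costs will be scaled by the pooled rate. Restricting costing to controls would discard roughly 107 of about 249 expected ill cases, when hospitalisations and evacuations are to be costed and the article already expects some provider data to be unobtainable.
- **The control arm is not an unbiased sample of travellers.** Online self-selection and the assumed 50% loss to follow-up remain.

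**Conclusion.** The point holds in a limited form. The plan does not say clearly which population supplies its base rate, and the source it names explicitly, all participants, estimates the rate without the video with a bias of half the true effect. Across the range examined this is 0 to 5 points. At the planned 40% versus 30%, the expected pooled rate is 35%, which is 12.5% too low in relative terms, and its 95% interval would include 40% only about one time in five. These figures assume a 40% control rate and 356 completers per arm.

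For cost, the same relative understatement follows only if a per-traveller or population figure is built on the pooled rate and cost per case is equal by arm. The document settles neither condition. A reader might conclude that both the incidence and the cost will certainly be wrong; that goes further than the text allows.

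These are descriptive secondary estimates. The randomised comparison of illness and the sample size are untouched.

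**What to change.** - **Data Analysis: Secondary Outcomes.** State that the headline cumulative incidence for Western Australian travellers to Bali comes from the control arm. Report the intervention arm separately, and label any pooled incidence as a sensitivity analysis. Name the arm in the closing sentence of the control-group paragraph, so that the two paragraphs no longer describe the same rate from different sources.
- **Strengths and Limitations.** Tie the base rates to that control-arm figure.
- **Cost-of-Illness Analysis.** State whether cost is per ill case, per traveller or for the population. Keep ill cases from both arms for cost per case, after checking that it is similar by arm. Multiply by control-arm incidence for any per-traveller or population figure.

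The cost is wording plus some precision: the 95% half-width for incidence goes from about 3.5 to 5.1 points. Data collection, sample size and the primary analysis do not change. The change does not remove bias from self-selection or loss to follow-up, and the report should say so.

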#### Recruitment

Recruitment will take place online, via advertisements promoting the Bali travel survey, strategically located on Facebook and Google pages. The advertisements will run for a 12-month study period to incorporate variation in travel across the year related to seasonal travel or university and school holidays. The advertisements will target people who have searched for Bali flights and/or accommodation online; this information is gathered by Facebook and Google through their single sign-on utility, as well as cookie data to track Internet activity. The main avenue for recruitment is the Internet because a previous study demonstrated that 87% of travelers to Bali make pretravel purchases—flights or accommodation—online [20]. Clicking on the advertisement will take people to a webpage, which briefly describes the study. People interested in enrolling in the study will be asked to enter their departure date, return date, sex, age range, and email address in an online form. This information will allow researchers to determine the age range and sex of those participants who later may be lost to follow-up. Participants will be asked to check a box to indicate that they consent to participate in the study. Travelers can only participate once in the study; multiple enrollments from the same email address will be blocked.

To assist with recruitment, participants will be offered an incentive of entering a lottery to win one AUD $1000 gift voucher or one of 10 AUD $100 gift vouchers. The winning names will be drawn upon study completion. Participants will be informed of the incentive via the online advertisement, consent page, and initial welcome email they receive.

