#### Posttravel Follow-Up

Within two weeks of the participants’ nominated return dates, they will receive an email containing a link to the posttravel survey, which will be optimized for mobile devices. The control and intervention groups will receive links to surveys that are almost identical, apart from the wording of one question on PTHA. For the intervention group, this question will be phrased to make it clear they are being asked about PTHA received external to this study (ie, PTHA from their general practitioner or from their own Internet search). If the participant does not complete the survey within a week, a second email will be sent to the participant.

The survey will contain questions in six general themes: (1) information about their trip to Bali, (2) PTHA behaviors, (3) risk prevention behaviors (sample question presented in Textbox 1), (4) knowledge about disease risk (sample question presented in Textbox 2), (5) illness and symptoms during and/or posttravel, and (6) basic demographic information. The survey was adapted from a 2014 WA traveler survey [20] and will take participants, on average, between 5 and 10 minutes to complete, depending on whether or not illness is reported. The final survey and intervention were developed in consultation with WA Department of Health staff and pilot-tested, with the intervention, by a focus group in late 2015.

Posttravel survey sample questions. Participants will be asked to report the health risk-prevention behaviors they engaged in during travel. Participants may choose from the following responses: Daily, Every 2-3 days, Once a week, and Never.Please answer the following questions about your behavior during your recent trip to Bali.How often did you use insect repellent on this trip?How often did you use alcohol-based hand sanitizer on this trip?How often did you use a mosquito net on this trip?How often did you use mosquito protective clothing on this trip? (eg, long sleeves)How often did you eat eggs with a runny yolk on this trip? (eg, fried egg on top of fried rice)How often did you eat fresh fruit you did not peel yourself on this trip?

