Posttravel survey sample questions. Participants will be asked to report their health risk knowledge posttravel. Participants may choose from the following responses: Agree, Disagree, and Unsure.The following questions concern your opinions on health risks while traveling.Please indicate whether you agree or disagree with each of the statements by ticking the appropriate box.The risk of someone catching measles in Bali is about the same as catching measles in Australia.Mosquitoes that bite during the daytime are a nuisance, but they do not transmit serious diseases.The ice from hotels in Bali is safe to serve in drinks.It is safe to feed monkeys at tourist venues in Bali.Salads (ie, uncooked fruits and vegetables) are safe to eat in Bali.You should seek urgent medical attention if you are bitten by a dog or other mammal in Bali.It is important to always use insect repellent when outdoors in Bali.If you are scratched or bitten by a monkey in Bali, you should receive treatment to prevent rabies.You should not eat eggs with runny yolks in Bali.

Participants who report seeking medical attention for a travel-related infection will be asked for permission to obtain specified health information relating to their illness from their health care provider. If consent is given, the participant will be asked to provide some identifying information including name, date of birth, name of medical practice or hospital visited, and the date of medical visit. Participants are advised that the information to be collected from the health care provider will include details regarding relevant diagnosis, laboratory tests, prescriptions, and, if admitted, length of stay. Letters will be sent to health care providers informing them that the participant has consented to participate in the study and that a WA Department of Health employee will contact them within the week by telephone. The WA Department of Health employee will conduct a phone interview with the health care provider using a uniform script. The self-reported data on diagnoses, health services accessed, and treatment will be validated against the health records.

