#### Data Analysis: Primary Outcome

Data analysis will be carried out using Epi Info version 7 (Centers for Disease Control and Prevention) and Stata version 12 (StataCorp LP).

The proportion of travelers in the control and intervention groups who self-report illness during their travels, or within two weeks of returning home, will be compared. A univariate analysis will be carried out using Pearson’s chi-square test for comparison of proportions and a *t* test for comparison of mean risk prevention behaviors and knowledge. Logistic regression analyses will be undertaken to estimate the impact of the intervention, while adjusting for other variables such as age, sex, and use of external PTHA, if differences between intervention and control groups are observed at the baseline. Intention-to-treat analysis will be undertaken.

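### Knowledge is measured only after travel, in the same survey as illness, so the planned regression cannot estimate its impact on illness risk

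*Protocol article*

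**What the plan says.** Under Data Analysis: Secondary Outcomes, the protocol article commits to a logistic regression for "The impact of demographic factors, risk prevention behaviors, and knowledge on the risk of travel-related illness symptoms in the study population". That is causal wording, with knowledge as a cause and illness as its consequence.

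The timing of the two measurements is set elsewhere in the article:

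- **Knowledge.** Under Posttravel Follow-Up: "Participants will be asked to report their health risk knowledge posttravel". The items are introduced with "The following questions concern your opinions on health risks while traveling" and ask for present opinions, not for recall of what was known before departure.
- **Illness.** It comes from the same questionnaire, whose themes include "4) knowledge about disease risk (sample question presented in Textbox 2), (5) illness and symptoms during and/or posttravel". Participants get it after the nominated return date, when "they will receive an email containing a link to the posttravel survey".
- **Illness window.** Under Data Analysis: Primary Outcome, travelers count as ill if they "self-report illness during their travels, or within two weeks of returning home".
- **Before travel.** Under Recruitment, people who enroll are "asked to enter their departure date, return date, sex, age range, and email address in an online form". Knowledge is not on that list.

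The Strengths and Limitations section does not mention the timing of the knowledge measurement.

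**The concern.** A regression can speak to the effect of knowledge on illness risk only if the knowledge score reflects what the traveler knew before falling ill. Here it reflects what the traveler believes when answering the survey. Three of the nine sample items concern ice, salads and runny eggs, and a traveler who had diarrhea may well revise those answers. Two more concern care after a bite or scratch, which a medical visit could teach. Since pretravel knowledge is never recorded, no adjustment in the analysis can recover it.

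Risk prevention behaviors, in the same model, are asked as trip-level frequencies with no timing relative to onset. Hand sanitizer taken up after falling ill on the trip cannot be told apart from sanitizer used beforehand.

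At stake is the reading of one secondary estimate. The article justifies the trial by the discordant results and methodological weaknesses of earlier observational studies. An estimate of the impact of knowledge that is open to reverse causation would put a similar weakness beside a randomized result. It could be read as showing that informed travelers do no better, or do worse.

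**Working it through.** **1. The plan's own figures.** The article computes nothing for this regression. Its sample size is used below and reproduces. With 40% versus 30%, two-sided alpha 0.05 and 80% power, n per arm = [1.96·√(2·0.35·0.65) + 0.8416·√(0.40·0.60 + 0.30·0.70)]² / 0.10² = (1.3221 + 0.5646)² / 0.01 ≈ 356. That gives 712 completers, and 712/(1 − 0.5) = 1424 enrolled. These figures are not in dispute.

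**2. Order of measurement.** Enrollment (no knowledge item), then the trip, then return, then one survey recording both illness and knowledge. An illness can be reported only if it has begun by the time of the survey, so knowledge is always measured after onset. When that knowledge was acquired is not observed.

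**3. Illustration with no true effect.** Assumptions, none of them from the documents: 50% know an item before travel; knowledge does not affect illness; a fraction g of the ill who did not know it learn it by the survey; a fraction h of the well do so.

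- Knowledge among the ill = 0.5 + 0.5g; among the well = 0.5 + 0.5h.
- With h = 0, observed OR = [(0.5 + 0.5g)/(0.5 − 0.5g)] / (0.5/0.5) = (1 + g)/(1 − g).

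| g (ill) | h (well) | Known, ill vs well | Observed OR |
|---|---|---|---|
| 0 | 0 | 50% vs 50% | 1.00 |
| 10% | 0 | 55% vs 50% | 1.1/0.9 = 1.22 |
| 20% | 0 | 60% vs 50% | 1.2/0.8 = 1.50 |
| 20% | 10% | 60% vs 55% | 1.50/1.22 = 1.23 |
| 20% | 20% | 60% vs 60% | 1.00 |
| 10% | 20% | 55% vs 60% | 1.22/1.50 = 0.81 |

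The bias depends on the difference in learning between ill and well, and reverses if the well learn more.

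**4. Illustration with a true protective effect.** Take a true OR of 0.70, 50% prior knowledge and 40% ill overall. The article "assumed an illness rate of 40% in the control group"; applying 40% to everyone is a simplification. Illness risk is then about 0.443 without and 0.357 with prior knowledge (mean 0.40; odds 0.556/0.795 = 0.70). With g = 20% and h = 0, the cells are:

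- ill, known: 0.5·0.357 + 0.5·0.443·0.2 = 0.223
- well, known: 0.5·0.643 = 0.321
- ill, not known: 0.5·0.443·0.8 = 0.177
- well, not known: 0.5·0.557 = 0.279

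Observed OR = (0.223·0.279)/(0.321·0.177) ≈ 1.09. At g = 10% it is 0.87. The association crosses 1 at g = (0.443 − 0.357)/[0.443·(2 − 0.443 − 0.357)] ≈ 16%.

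**5. Visibility at the planned size.** In 2000 simulated trials of 712 completers, with no true effect, 40% ill and h = 0, an unadjusted comparison gave a significant result in the direction of knowledge raising risk in about 24% of trials at g = 10% and 74% at g = 20%. With g = 0 the figure was about 2%.

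**The case against.** The strongest objection is that measuring knowledge after illness does not show that it was acquired after illness. A reader might infer that the order in time is reversed. The documents do not support that: posttravel answers may be a fair proxy for pretravel knowledge, and the order is indeterminate. This stands, and it limits the point to what the coefficient can identify.

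The size is assumed throughout. The 50% prior knowledge, the learning fractions and the absence of a true effect come from no document, and learning among the well shrinks the bias or reverses it. The illustration also concerns a single item. The primary-outcome section speaks of comparing mean knowledge, which suggests a score, and a gastrointestinal illness would not obviously teach the measles or mosquito items. All of this stands; the odds ratios show how little learning would matter for one item and do not forecast the trial's result.

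A reader might also infer that the behavior estimates are equally compromised. They are not: behaviors refer to the trip, and for illness that began after return they come first.

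A reader might count the absence of allocation from the description of this model as a defect. An article commonly leaves such covariate detail to the analysis plan, so it is no finding.

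Finally, this regression is not among the outcomes listed in the Abstract or the Overview. That limits the consequence, but the planned causal reading still lacks support from the design.

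**Conclusion.** The point holds as a limit on what this secondary regression can show. With one posttravel measurement and no pretravel one, its knowledge coefficient mixes any effect of knowledge on illness with any learning caused by illness, and no reanalysis of the planned data can separate them. Reading it as an impact would be sound only if illness left the answers unchanged, or if ill and well travelers learned alike. The design can check neither.

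The size of the bias is unknown. On the stated assumptions for a single item, 10% to 20% learning among the ill alone gives a spurious odds ratio of 1.22 to 1.50, and would move a true odds ratio of 0.70 to between 0.87 and 1.09. A wrong sign is therefore possible, but the documents do not show that it will occur. Behaviors share the weakness only for illness that began during the trip.

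A reader should not carry this over to the trial's main results. The randomized comparison of illness, and the comparisons of posttravel knowledge and behaviors by arm, do not depend on this model.

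**What to change.** Do not estimate an impact of posttravel knowledge on illness. Either of two changes to the analysis wording would do:

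- leave knowledge out of the illness-risk model and keep it as an outcome compared by arm; or
- report knowledge, and behaviors with it, only as cross-sectional associations with illness, and state possible reverse causation as a limitation.

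If allocation is included in a model that also contains behaviors or knowledge, its coefficient should not be read as the intervention effect. The video is meant to change both, so such a model conditions on steps between the intervention and illness.

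The cost is wording, with no new data and no change to the sample size. The downside is that one exploratory secondary estimate is dropped or relabelled. Adding knowledge items at enrollment would give the missing pretravel measure, but the questions could themselves prompt participants in both arms, so this is not a free alternative.

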**Methods:**

Western Australian travelers to Bali will be recruited online before departure and will be randomly allocated to an intervention or control group by computer algorithm. The intervention in this study is a short animated video, with accompanying text, containing PTHA relevant to Bali. An online posttravel survey will be administered to all participants within two weeks of their return from Bali. The primary outcome is the difference in self-reported travel-related illness rates between control and intervention groups. Secondary outcomes include the difference in risk prevention behaviors and health risk knowledge between the control and intervention groups. Further secondary outcomes include whether individuals in the control group who sought external PTHA differ from those who did not with respect to risk prevention behaviors, health risk knowledge, and health risk perception, as well as the rate of self-reported travel-related illness.

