### Study Outcomes and Data Analysis

#### Overview

The primary outcome of the study is a difference in self-reported overall travel-related illness between the intervention and control groups. Secondary outcomes are differences in risk prevention behaviors (Textbox 1) and health risk perceptions (Textbox 2) between the intervention and control groups. The economic cost of travel-related illness symptoms in returning travelers from Bali will also be estimated.

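### The pooled risk-factor regression names no term for randomized arm, so any video effect outside the modeled factors can be credited to knowledge or behavior items

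*Protocol article*

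**What the plan says.** All places are in the Protocol article.

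- **Data Analysis: Secondary Outcomes, first paragraph.** It opens with "Data from all participants will also be used" for the cumulative incidence of symptoms. It then plans a logistic model for "The impact of demographic factors, risk prevention behaviors, and knowledge on the risk of travel-related illness symptoms in the study population". Three predictor groups are named, and arm is not one of them.
- **Same section, next paragraph.** "Data from the control group will be used to assess further secondary outcomes". The restriction to controls starts here, so the regression before it reads as covering both arms.
- **Overview.** The primary outcome is the between-arm difference in self-reported illness. "Secondary outcomes are differences in risk prevention behaviors (Textbox 1) and health risk perceptions (Textbox 2) between the intervention and control groups".
- **Abstract, Methods.** "Secondary outcomes include the difference in risk prevention behaviors and health risk knowledge between the control and intervention groups".
- **Data Analysis: Primary Outcome.** A separate model does include arm: "Logistic regression analyses will be undertaken to estimate the impact of the intervention".
- **Posttravel Follow-Up.** Behaviors, knowledge and illness are all collected in one survey after travel.

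**The concern.** Allocation is 1:1, so about half of the pooled sample is assigned to a video meant to change what travelers know, what they do and how often they fall ill. In a regression of illness on knowledge and behavior, arm can move both sides. That makes it a potential confounder created by the trial itself and known for every participant.

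Suppose the video lowers illness partly by a route that the modeled items do not capture, or capture with error. An item that the video teaches, but that does nothing by itself, will then tend to look protective, because video recipients score higher on it and are ill less often. If the video instead prompts people to report more symptoms, the distortion runs the other way. The stake is the reading of single items: which pieces of advice appear to prevent illness.

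**Working it through.** **Inputs from the article.** Sample Size Calculation: 40% illness in controls, a reduction of 10%, 80% power, P value of .05, 356 completers per arm (712 in all). Randomization: 1:1.

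**Inputs assumed.** The article gives no figure for how far the video moves knowledge or behavior. I use a score with SD 1 within arm, raised by d = 0.2, 0.5 or 0.8 SD in the video arm.

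**1. The plan's own figure.** Reading the reduction as 10 percentage points, two-sided, without continuity correction:

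n per arm = [1.960·√(2·0.35·0.65) + 0.842·√(0.40·0.60 + 0.30·0.70)]² / 0.10² = 355.9, so 356.

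This matches the stated 356, and 712 / 0.5 = 1424 enrolled. The point made here does not touch that calculation. It only takes 40% v 30% and 712 from it.

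**2. The video effect on the log-odds scale.** T = ln(0.30/0.70) − ln(0.40/0.60) = −0.847 + 0.405 = −0.442, an odds ratio of 0.64.

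**3. No effect through the score (true odds ratio 1.00), arm omitted.** With 1:1 allocation the covariance of arm and score is d/4, and the pooled variance of the score is 1 + d²/4. Approximately:

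- coefficient b = T·(d/4)/(1 + d²/4)
- standard error = 1/√[712·0.35·0.65·(1 + d²/4)]
- rejection rate = Φ(|b|/SE − 1.96) + Φ(−|b|/SE − 1.96)

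| d | b | SE | odds ratio | rejection rate |
|---|---|---|---|---|
| 0.2 | −0.022 | 0.078 | 0.98 | 5.9% |
| 0.5 | −0.052 | 0.076 | 0.95 | 10.5% |
| 0.8 | −0.076 | 0.073 | 0.93 | 18.1% |

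Fitted logistic models on simulated data agree: odds ratios of 0.98, 0.95 and 0.92 to 0.93, with error rates of about 6%, 10% and 17 to 19%. With arm in the model the odds ratio returns to 1.00 and the error to about 4 to 6%.

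**4. Some or all of the effect through the score** (simulated odds ratios per SD, for d = 0.2 / 0.5 / 0.8):

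| Share through the score | true | arm omitted | arm included |
|---|---|---|---|
| half | 0.33 / 0.64 / 0.76 | 0.33 / 0.63 / 0.73 | 0.33 / 0.64 / 0.76 |
| all | 0.11 / 0.41 / 0.58 | 0.11 / 0.41 / 0.58 | 0.11 / 0.41 / 0.58 |

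With full mediation through a perfectly measured score there is no bias. With half, the shift is small.

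**5. A second taught item with no effect of its own.** Let the whole video effect run through one factor, and let the video also raise an inert item, each by 0.5 SD.

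- Inert item tested alone, arm omitted: odds ratio about 0.95, error about 10%.
- Both modeled, active factor measured with an assumed reliability of 0.5, arm omitted: odds ratio about 0.97, error about 7%.
- Both modeled, active factor measured perfectly: no inflation.
- Arm added in the first two cases: odds ratio 1.00, error about 5%.

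**6. Price of the arm term.** At d = 0.5 the standard error rises from 0.077 to 0.080.

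**The case against.** **The sentence names factors of interest, not a full model.** A condensed article may leave the covariate list to the full plan. This stands in part. A reader might infer that the plan excludes arm, but the article does not say so. What remains is that it states a population and a set of predictors, and the model so stated lacks a term it should have. If the full plan already adds arm, the remedy is one clause.

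**The video is supposed to work through knowledge and behavior.** A reader might infer that pooling necessarily hands the video's effect to those factors in error. The article does not support that. If the video acts wholly through modeled, well-measured factors, the credit is correct and omitting arm does no harm (step 4). The bias is conditional. It is still a live possibility: illness is self-reported, so advice may alter reporting. Behaviors are recalled on four response options and knowledge is scored Agree, Disagree or Unsure, so measurement error is likely.

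**Particular unmeasured routes cannot be shown.** The textboxes contain sample questions only, and the knowledge items already touch on monkeys, dog bites and measles. This stands: one cannot claim from the article that animal contact or vaccination checks go unasked.

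**Large figures need extreme inputs.** Error rates above 20% require a shift of about 1 SD with no mediation at all. Nothing in the article supports such a shift, so those figures should not be used as the size of the problem.

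**Other weaknesses are larger.** Reverse causation and recall remain with or without arm, because exposures are reported after travel. This also stands.

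**Conclusion.** The point holds in a limited, conditional form. As stated, the all-participant risk-factor model has no arm term, although the trial tests whether arm changes both the predictors and the outcome. Where the video acts partly outside the modeled or well-measured factors, some of its effect can be assigned to individual items.

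The size is modest. With no mediation, a null odds ratio of 1.00 per SD reads as about 0.98 to 0.95, with type I error of about 6 to 10%, for shifts of 0.2 to 0.5 SD; only larger assumed shifts give more. These figures rest on the planned 40% v 30% effect being realized, 712 completers, a single continuous score and assumed shifts. They show a range and do not estimate this trial's bias.

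The analysis is secondary and observational. A reader might take the point as a threat to the main result. It is not: the randomized comparison, the primary outcome and the sample size are unaffected.

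**What to change.** In Data Analysis: Secondary Outcomes, state that randomized arm is a covariate in every all-participant model relating demographics, behaviors or knowledge to illness symptoms. A fit in the control arm alone can be added as an optional sensitivity check. It rests on about half the completers (356 of 712 as planned), so it is less precise and should not replace the pooled model.

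The arm term uses a variable already held, and needs no extra participants or data. It costs one degree of freedom and a slightly larger standard error. Two limits should be reported with the results. The arm coefficient in this model is adjusted for factors measured after randomization, so it is not the trial's intervention effect. The knowledge and behavior coefficients remain observational associations, because both are reported after travel.
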